### Data Analysis

#### Sample Size Calculation

Testing the primary outcome using two sided t-testing will require at least 224 dyads (patients and caregivers) to complete the study (112 per arm). This sample size affords 80% power to detect a difference as small as 0.33 standard deviations in mean summed symptom severity (Hypothesis 1) and social support (Hypothesis 2) between arms using 0.05 as the level of significance. This consistent with standards for clinical relevance and those seen in similar interventions [26,42]. Moreover, this sample size is sufficient to accommodate longitudinal analyses with repeated measures. To account for 25% attrition (consistent with prior trials of ATSA) and ensure that 112 dyads in each group are available for analysis, the goal is to enroll 300 dyads in the trial [26].

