#### Hypothesis Testing

We will compare summed symptom scores at 10 weeks between the control and intervention groups using a multiple regression model. The model will include a dummy variable for study group assignment as the main independent variable and will be adjusted for baseline symptom scores. While we do not expect the groups to be unbalanced with respect to other potential predictors of the outcome, we will adjust for these if randomization is not fully successful. The parameter estimate of the group assignment dummy variable and its statistical significance will estimate and test for the outcome difference between the two study groups at week 10, adjusting for baseline values of the outcome. A similar approach will be used to test the intervention effect on secondary outcomes (namely physical functioning, service utilization, and chemotherapy adherence). To determine if there is maintenance of the intervention effects on each outcome, we will use a similar regression model using the corresponding measurements at week 14, and a longitudinal model for the outcomes at 10 and 14 weeks.

Our analytic approach for testing Hypothesis 2 will be similar to that described above. We will use multiple regression models to compare group differences in patient-reported social support scores as measured by the Inventory of Socially Supportive Behaviors at 10 weeks, adjusting for baseline values of the ISSB [38]. The model will include a dummy variable for study group assignment as well as the baseline value of the ISSB scores, and the parameter estimate of the dummy variable will estimate the intervention effect on caregivers at 10 weeks. A similar approach will be used to test the intervention effect on caregiver burden and distress.

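### The stated sample size inputs give about 69% power at 0.33 SD with a two-sided t-test, not 80%

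*Protocol article*

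**What the plan says.** The Sample Size Calculation section of the protocol article fixes every input of a two-group comparison.

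- Test and number: "Testing the primary outcome using two sided t-testing will require at least 224 dyads", which it splits as 112 per arm.
- Power and effect: "This sample size affords 80% power to detect a difference as small as 0.33 standard deviations in mean summed symptom severity". The same sentence extends the claim to social support (Hypothesis 2).
- Type I error: "using 0.05 as the level of significance".
- Attrition: 25%, which takes 224 completers to an enrolment goal of 300 dyads.

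The section gives no baseline-to-follow-up correlation, no between-visit correlation and no other variance reduction. It says only that the number is enough to accommodate longitudinal analyses with repeated measures.

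The analysis itself is set out under Hypothesis Testing: "We will compare summed symptom scores at 10 weeks between the control and intervention groups using a multiple regression model". That model adjusts for the baseline symptom score. The model for patient-reported social support, measured with the Inventory of Socially Supportive Behaviors (ISSB), adjusts for its own baseline in the same way.

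**The concern.** For a two-sided 5% test, 112 per arm is too few for 80% power at a third of a standard deviation. Because the difference is already in SD units, no variance assumption can reconcile the figures. Sidedness, alpha, number, effect and power are printed together, so this is not detail that an article leaves to a fuller protocol or analysis plan.

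At stake is what the trial can claim to detect. The section presents 0.33 SD as in line with standards for clinical relevance and with similar interventions, so an overstated power falls on the effect the trial treats as worth finding. It affects both the primary outcome and Hypothesis 2.

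**Working it through.** **Inputs**, all from the Sample Size Calculation section: d = 0.33 (SD = 1), n = 112 per arm, alpha = 0.05, two-sided, target power 80%, attrition 25%.

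**Step 1. Try to reproduce the stated 80%.** Normal approximation: power = Φ(d·√(n/2) − z).

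- d·√(n/2) = 0.33 × √56 = 0.33 × 7.483 = 2.470.
- Two-sided, z = 1.960: Φ(0.510) = 69.5%. The exact noncentral t (222 df) gives 69.1%.
- One-sided, z = 1.645: Φ(0.825) = 79.5%. The exact noncentral t gives 79.3%.

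The stated figure is not reproduced under the stated two-sided test. It is nearly reproduced under a one-sided 5% test.

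**Step 2. Difference detectable with 80% power at 112 per arm.** d = (z + 0.842)·√(2/n), with √(2/112) = 0.1336.

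- Two-sided: 2.802 × 0.1336 = 0.374; exact t 0.376.
- One-sided: 2.486 × 0.1336 = 0.332; exact t 0.333.

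**Step 3. Number needed for 80% power at 0.33 SD.** n = 2(z + 0.842)²/d², with d² = 0.1089.

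- Two-sided: 2 × 7.849/0.1089 = 144.1, so 145 per arm; exact t 146 (292 completers).
- One-sided: 2 × 6.183/0.1089 = 113.5, so 114 per arm; exact t 115.

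**Step 4. Could rounding or attrition explain it?**

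- If 0.33 is a rounded 0.335, two-sided power is still only 70.8% (normal) or 70.4% (exact t).
- The attrition step is correct: 224/0.75 = 298.7, or about 300.
- Analysing all 300 (150 per arm) would give 81.5% (normal) or 81.3% (exact t). But the section bases its claim on the 112 per arm left after attrition.

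**Step 5. The planned baseline-adjusted regression.** Adjustment replaces d by d/√(1 − r²), where r is the correlation between baseline and week 10. The article gives no value, so r is an assumption here. Two-sided, 112 per arm, 0.33 SD, normal approximation:

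| Assumed r | Power | Chance of missing 0.33 SD |
|---|---|---|
| 0 | 69.5% | 30.5% |
| 0.3 | 73.5% | 26.5% |
| 0.4 | 76.9% | 23.1% |
| 0.5 | 81.4% | 18.6% |
| 0.6 | 87.0% | 13.0% |

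Power reaches 80% at r of about 0.47 (about 0.48 by exact t).

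**Step 6. Averaging weeks 10 and 14.** The SD becomes √((1 + ρ)/2), where ρ is the between-visit correlation, again an assumption. Power is 81.4% at ρ = 0.5, 80.1% at 0.55, 78.8% at 0.6 and 76.4% at 0.7. The article takes the primary effect from week 10, so this average is not the primary comparison.

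**The case against.** The best defence is that the t-test is only a planning device. The primary model adjusts for baseline, and longitudinal models are also planned. Sizing on an unadjusted t-test and then adjusting for baseline is a common simplification that normally errs on the safe side, so it is not a defect in itself. Steps 5 and 6 show that the planned analyses could reach 80% with 112 per arm. This stands as a limit on the consequence. It does not rescue the sentence, which attributes its number to two-sided t-testing and states neither correlation.

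A reader might also infer three stronger things that the document does not support.

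- **That a one-sided test was used.** The numerical match is close, but the article says two-sided and nothing else. The match suggests an explanation and does not document one.
- **That the trial will miss a true 0.33 SD effect 31% of the time.** That rate (100% − 69.1%) belongs to the unadjusted t-test. For the planned regression it is roughly 13% to 27% if r lies between 0.6 and 0.3, and no r is documented.
- **That 0.33 SD can be kept by assuming r of at least 0.48.** Nothing in the article supports that value. Nor is there a reason for the symptom score and the ISSB, which are different instruments, to share one correlation.

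**Conclusion.** The power statement is wrong as written. Under its own inputs, power at 0.33 SD is about 69%, some 11 points below the stated 80%. The difference detectable with 80% power is about 0.38 SD (0.376/0.33 = 1.14, so 14% larger than stated), and 0.33 SD would need 146 completers per arm against the 112 planned. No other part of the article corrects this. The same shortfall applies to social support, which shares the sentence.

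This conclusion needs no assumption beyond equal arms and the printed inputs, and it does not depend on how the error arose. What remains uncertain is the power of the analysis that will actually be run. It may be adequate, but that depends on correlations the article does not give.

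**What to change.** Keep the enrolment goal of 300 dyads and restate the power sentence along these lines: *With a two-sided t-test at the 0.05 level, 112 completers per arm give 80% power for a difference of 0.38 SD, and 69% power for 0.33 SD.* Make the same correction for social support.

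If power for the baseline-adjusted regression is also quoted, give it as a range over assumed baseline-to-week-10 correlations: for 0.33 SD, about 73% at r = 0.3, 77% at 0.4, 81% at 0.5 and 87% at 0.6. State the assumed correlation separately for symptom severity and for the ISSB.

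This is a change of wording and needs no extra dyads. The price is that the stated detectable effect becomes slightly less favourable. Keeping 80% power at 0.33 SD on the t-test alone would instead need 292/0.75 = 389.3, or about 390 enrolled dyads.

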#### Preliminary Analysis

Graphical analyses will include: (1) examining distributions of the various numerical outcome variables using box plots and histograms to investigate skewness, gaps and outliers; (2) side-by-side box plots and back-to-back histograms to graphically rule out baseline differences in outcomes between the two study groups; (3) plots of cross-sectional outcome means over time to assess the longitudinal trends within and between the two arms; and (4) scatter plots of change in outcome variables versus change in potential mediator variables. Variables with highly skewed distributions will be transformed. When such transformations are not successful, we will employ generalized linear models in the primary analyses. In addition, we will consider dichotomizing the variables using clinically-relevant cut points.

#### Baseline Analysis

We will test for possible baseline differences in the outcomes and characteristics of the patients and caregivers in the two study groups including but not limited to: patient and caregiver socio-demographic and clinical characteristics, symptom scores, physical and mental functioning, social support, caregiver relationship type (spouse vs. other), and caregiver location (in-home vs. out-of-home). If any significant baseline differences are identified, intervention effects will be estimated using multivariable analysis adjusted for baseline variables as well as stratified analysis using propensity scores.

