## Methods

The intervention's efficacy is being evaluated using a randomized, controlled trial among patients undergoing a course of chemotherapy at two Department of Veterans Affairs (VA) oncology clinics located in Ann Arbor, MI and Fargo, ND. Three hundred patients with solid tumors undergoing chemotherapy and reporting at least one core symptom at a moderate level are being assigned to either 10 weeks of weekly ATSA contacts or 10 weeks of weekly ATSA contacts plus caregiver alerts and access to the Cancer CarePartners website. The duration and intensity of the intervention is premised on past work suggesting that ATSA's benefits peak at 10 weeks [11].

The goal of the study is to determine if, when compared to a comparison group receiving ATSA alone, patients who receive ATSA and whose caregivers receive access to Cancer CarePartners will report: significantly less total symptom severity; and secondarily improved physical functioning, adherence to chemotherapy, and more appropriate utilization of health services at 10 weeks. The study also will determine whether caregivers provide more social support and report less caregiver burden and distress.

Patients and caregivers will be surveyed at intake, 10, and 14 weeks. Further, we will track patient participation with ATSA and (in the experimental arm) caregiver use of the Website and social support provided, allowing for indicators of intervention dose to be incorporated into our analyses. Finally, all patients will receive routine oncology, hospice, and/or palliative care.

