After completing the baseline assessment, participating patients are randomized to either the control or intervention arm by a computer minimization program that balances the arms for type of cancer (lung vs. other) and the type of caregiver (in-home vs. out of home). The minimization procedure, known as 'adaptive randomization' balances trial arms according to the history of previous allocations. Arms are being balanced for lung cancer since patients with lung cancer have a symptom pattern distinct from patients with other solid tumors [34,35]. Arms are being balanced for type of caregiver because in-home caregivers have more access to the patient than do caregivers living at a distance and, hence, more opportunities for providing support.

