#### Attrition Analyses

To ensure the validity of findings, baseline characteristics of patients and caregivers who drop out of the study will be compared by study group. We will also summarize and compare reasons for attrition. If any differences are found, the appropriate covariance adjustments or propensity score stratifications will be employed in the primary analysis. To ensure the generalizability of our findings, we will also compare the baseline characteristics of those completing the study against those of subjects who drop out.

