#### Missing Data

When missing values occur, we will determine whether missingness is random or associated with patient or caregiver characteristics using standard regression models. As long as we do not observe any bias in patterns of dropout or missing data (see attrition analysis above), we will use regression techniques allowing for missing at random. Models will include 10 and 14 week assessment data as longitudinal outcome values, an intervention effect indicator, and baseline values of the outcome variable and other covariates as fixed independent variables. If the analyses indicate that missingness depends on unobserved outcome values(, we will account for missing data using a pattern mixture model [43]. This technique allows the use of data from all participants (not just completers) and provides an unbiased intervention effect estimate.

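### Beyond the baseline symptom score, covariates enter the primary model only when an observed difference triggers them, and the two minimisation factors are left out

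*Protocol article*

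**What the plan says.** The Hypothesis Testing section gives the primary comparison as a regression of the week-10 summed symptom score: "The model will include a dummy variable for study group assignment as the main independent variable and will be adjusted for baseline symptom scores". The baseline score is therefore a fixed term. Other covariates reach this comparison by three conditional routes:

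- **Baseline Analysis:** "If any significant baseline differences are identified, intervention effects will be estimated using multivariable analysis adjusted for baseline variables", together with an analysis stratified by propensity score. The list of variables to be tested is open-ended.
- **Attrition Analyses:** after comparing the arms on the characteristics of those who drop out, "If any differences are found, the appropriate covariance adjustments or propensity score stratifications will be employed in the primary analysis". No threshold is given.
- **Hypothesis Testing:** for other potential predictors, "we will adjust for these if randomization is not fully successful". No criterion is given. The Quality control section describes quarterly comparisons of the arms but does not say what result would count as failure.

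Recruitment & Randomization describes a minimisation program that "balances the arms for type of cancer (lung vs. other) and the type of caregiver (in-home vs. out of home"). Neither factor is named in the primary model. The second reappears in Baseline Analysis only as one of the variables to be tested, "caregiver location (in-home vs. out-of-home"). The Missing Data section describes a longitudinal model with "baseline values of the outcome variable and other covariates as fixed independent variables", but does not name the other covariates. Patients come from "two Department of Veterans Affairs (VA) oncology clinics located in Ann Arbor, MI and Fargo, ND". Site is neither a minimisation factor nor a term in the stated model.

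**The concern.** There are two linked problems.

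First, the primary model is not settled until the arms have been compared. A significant baseline difference between randomised groups arises by chance and carries no information on whether the variable predicts outcome. A rule built on it adjusts for whatever happens to be unbalanced. When a trigger fires, the plan yields a covariate-adjusted estimate, a propensity-stratified estimate, or both, and does not say which carries the primary conclusion.

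Second, the sponsor thought two factors important enough to balance by design, yet the stated model leaves them out. Minimisation reduces the true sampling variance of the treatment difference. A model without those factors does not recognise that reduction, so to the extent that they predict outcome beyond the baseline score, its standard error is too large. Because balance is forced, a balance test is the one route by which these factors are least likely to enter.

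At stake are a clear single primary estimate and some power.

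**Working it through.** **1. What is fixed and what is conditional**

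| Term | Status in the week-10 primary model |
|---|---|
| Arm | always |
| Baseline summed symptom score | always |
| Lung vs other cancer | only if triggered |
| In-home vs out-of-home caregiver | only if triggered |
| Site | only if triggered |
| Other baseline variables | only if triggered; list open |

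**2. How often the baseline trigger fires by chance**

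For k independent tests at 5% under correct randomisation, the chance of at least one significant result is 1 − 0.95^k. The number of tests is an assumption, because the list is open.

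| k | 8 | 10 | 15 | 20 | 30 |
|---|---|---|---|---|---|
| Chance | 34% | 40% | 54% | 64% | 79% |

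Correlated variables would lower these figures.

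**3. The plan's own sizing**

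Sample Size Calculation gives 224 completers (112 per arm), 0.33 SD, two-sided 0.05 and 25% attrition. The attrition step reproduces: 224 / 0.75 = 298.7, hence 300. An unadjusted two-sided comparison of 112 per arm at 0.33 SD has about 69% power, not 80%. That is a separate matter; it is given here because the stated model is baseline-adjusted and so has a different starting point.

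**4. Cost of omitting the minimisation factors**

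Assumed, not in the documents: a baseline–outcome correlation of 0.5, leaving residual variance 1 − 0.25 = 0.75; factor prevalences 0.4 and 0.6; and each factor shifting the outcome by b beyond the baseline score. The factors then add V = b²(0.4×0.6 + 0.6×0.4) = 0.48b² to the residual variance. The signal is 0.33 × √(112/2) = 2.469.

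- Factors included: power = Φ(2.469/√0.75 − 1.96) = Φ(0.89) = 81.4%.
- Factors omitted: the true variance stays at 0.75 because the arms are balanced, but the model estimates 0.75 + V. Power = Φ((2.469 − 1.96√(0.75 + V))/√0.75), and type I error = 2(1 − Φ(1.96√((0.75 + V)/0.75))).

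| b | V | Power, included | Power, omitted | Type I error, omitted |
|---|---|---|---|---|
| 0 | 0 | 81.4% | 81.4% | 5.0% |
| 0.25 | 0.03 | 81.4% | 80.3% | 4.6% |
| 0.5 | 0.12 | 81.4% | 77.1% | 3.5% |

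Suppose a site effect of b = 0.5 (assumed prevalence 0.35) is omitted too. It adds 0.25 × 0.35 × 0.65 = 0.057 to both variances, since site is not balanced by design. Power is then Φ((2.469 − 1.96√0.927)/√0.807) = 74.2%, a loss of about 7 points.

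**5. Check by simulation** (3,000 trials per setting, 224 completers, minimisation on two factors, same assumptions, site effect included)

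| b | Baseline score only | Factors and site always in | Test-triggered covariates |
|---|---|---|---|
| 0 | 81% | 82% | 82% |
| 0.25 | 79% | 81% | 79% |
| 0.5 | 74% | 81% | 74% |

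Simulation error on power is about 0.7–0.8 points. At b = 0.5 the type I errors are 4.0%, 5.2% and 3.3% respectively (error about 0.4 points). The test trigger does not recover the lost power.

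**6. Overlap with the baseline score**

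In a further simulation (4,000 trials, correlation 0.5) the factors explain 10% of outcome variance. Power with the factors omitted against included is 81.3% vs 81.0% if the baseline score already carries all of that 10%, 83.8% vs 84.4% if it carries half, and 81% vs 85% if it carries none. At 15% the losses are about 0, 1.4 and 5 points.

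**The case against.** The strongest defence is that the default model is named, always adjusts for what is probably the best single predictor, and at worst errs on the conservative side. Analysts are stated to be blinded to arm. Lung-cancer symptoms should already show in the baseline score, so the power loss may be negligible. The protocol justifies the caregiver factor by opportunity to give support, not by symptom prognosis. All of this stands, and it limits the size of the point. It does not settle which estimate is primary once a trigger fires.

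Four stronger readings are tempting, and the documents do not support them:

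- **That no covariate is pre-specified.** The baseline symptom score always is.
- **That the rule inflates type I error.** Following it as written gave error below 5% in the simulation. Figures of about 7.6% to 8.5% arise only if the most favourable of three analyses may be chosen freely, one of them unadjusted. The plan offers neither that freedom nor an unadjusted model.
- **That power is about 70%, against 74–76% with the factors.** Those figures match a model without the baseline score, which is not the stated one.
- **That the attrition comparison should go too.** Dropout happens after randomisation, so differences there can be real, and adjusting for predictors of dropout fits the missing-at-random approach in Missing Data. The chance-imbalance argument does not reach it.

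Nor does the minimisation argument extend to site, which was not balanced by design.

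**Conclusion.** The point holds in limited form. Beyond the baseline score, the content of the primary model depends on observed differences, by a rule that does not identify prognostic covariates, and two methods of adjustment are left unranked. The two minimisation factors are omitted and would almost never enter through a balance test.

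The omission makes the test somewhat conservative. It costs from about 0 to about 5 points of power for the two factors, and about 7 if an equally strong site effect is left out as well. These sizes rest on assumed prognostic strength, prevalences and a baseline–outcome correlation of 0.5, none of which the protocol gives. The chance of a false baseline trigger rests on an assumed number of independent tests. Because the protocol states these rules itself, they are not detail left to an analysis plan. The matter should be corrected, but it does not undermine the validity of the stated default test.

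**What to change.** - Pre-specify one primary model: week-10 summed score on arm, baseline summed score, cancer type (lung or other) and caregiver type (in-home or out-of-home). Site may be added but is optional.
- Use the same factors for the other outcomes, with the matching baseline value.
- In Baseline Analysis, remove the significance trigger as a route into the primary analysis and present baseline comparisons descriptively.
- In Hypothesis Testing, remove the clause that makes adjustment depend on whether randomisation succeeded.
- Keep the comparison in Attrition Analyses, but label any dropout-driven adjustment or propensity stratification as a sensitivity analysis.

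The cost is a change of wording and two degrees of freedom, or three with site. No new data are needed: both minimisation factors are recorded for allocation, and the clinic is known.
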